| --- | --- | --- | --- |
| **Outcome measure** | **Recommended frequency** | **Recommended Age** | **Grade^±^** |
| Vaccinations[^52^](#_ENREF_52) |  |  |  |
| Influenza[^146^](#_ENREF_146) | Yearly | 6 months of age or older |  |
| Herpes zoster (shingles)[^147^](#_ENREF_147) | Once (2 doses) | 50 or older |  |
| Pneumococcal (PCV20; PPSV23)[^148^](#_ENREF_148) | Once | 65 and older regardless of previous vaccination history |  |
| Tetanus (Td or Tdap)[^149^](#_ENREF_149) | Booster every 10 years | 19 and older |  |
| Cancer screening |  |  |  |
| Colorectal cancer | Every 1-10 years depending on type of screening | 45-49 years  50-75  76-85 | B  A  C |
| Mammogram | Every 2 years | Women 50 to 74 years  75 or older | B  I |
| Pap smear | Every 3-5 years | Women 21-65 years  Older than 65 | A  D |
| PSA (prostate) | Individualized decision (55-69)  Not recommended if >=70 | Men aged 55-69  Men 70 and older | C  D |
| Other screening |  |  |  |
| Ultrasound for abdominal aortic  aneurysm[^28^](#_ENREF_28)^,^[^45^](#_ENREF_45)^,^[^46^](#_ENREF_46) | Once | Men ages 65-75 who have ever smoked | B |
| Bone densitometry | At least once | Women aged 65 and older | B |
| Hepatitis C[^150^](#_ENREF_150) | Once | 18-79 | B |
| Alcohol misuse | Yearly | 18 or older | B |
| Tobacco use | Yearly | All adults | A |
| Depression[^151^](#_ENREF_151) | Yearly | All adults | B |
| Advance care planning[^66^](#_ENREF_66)^,^[^67^](#_ENREF_67) |  |  |  |
| ***** Based on USPSTF, CDC/ACIP guidelines,[^152-154^](#_ENREF_152) will adjust as needed to match guidelines at the time of data collection  ± A=recommended (high certainty of substantial net benefit); B=recommended (high certainty of moderate net benefit or moderate certainty of moderate to substantial net benefit); C=selectively offer based on professional judgement and patient preferences (moderate certainty of small net benefit); D=recommends against service (no net benefit or harms outweigh the benefits); I=current evidence is insufficient to assess balance of benefits and harms | | | |

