## 10 STATISTICAL CONSIDERATIONS

### 10.1 Statistical Hypothesis

- ***Primary Endpoints***:

We hypothesize that the intervention (PT-AWV intervention) will result in:

- 1. greater AWV utilization (% of eligible patients completing an AWV or IPPE in the past 12 months) at 12, 18 and 24 months after intervention implementation
  2. patients being up to date on a greater percentage of their total number of recommended services (of a maximum of 12 recommended services per patient) at 12, 18 and 24 months after intervention implementation;

We also hypothesize that the PT-AWV intervention will reduce racial/ethnic disparities in AWV utilization. Alternatively, our null hypotheses are that there will be no difference in AWV or USPSTF and CDC/ACIP-recommended service utilization with implementation of the PT-AWV intervention and that there will be racial/ethnic disparities in AWV utilization.

- ***Secondary Endpoint***(s):

We hypothesize that the PT-AWV intervention will result in a greater percentage of patients who are up to date on each of the individual preventive health services listed in [Section 4.0](#_4_OBJECTIVES_AND) **Table 2**. Alternatively, our null hypothesis is that there will be no difference in utilization in the USPSTF and CDC/ACIP-recommended services examined.

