| Colon cancer | 51-75 years of age | % of patients 50-75 with appropriate colon cancer screening  1) Fecal occult blood test within past 12 months  2) Flex sig within the past 5 years  3) Colonoscopy within the past 10 years  4) CT colonography within the past 5 years  5) FIT-DNA test within the past 3 years | lab_fobt  lab_ifobt_fit  proc_flexible_sigmoidoscopy  proc_colonoscopy  proc_colon_ca_scrn_adenoma  proc_ct_colonography  lab_stool_dna_cologuard | pmh_colorectal_cancer  pmh_total_colectomy  doc_hospice  dx_palliative  dx_frailty  dx_advanced_illness |
| Prostate specific antigen | Men aged 70 years and older | % men 70 and over who were screened for prostate cancer  PSA based screening test performed during the measurement year | gender_male  lab_psa  lab_psa_free | pmh_cancer_prostate  *PSA test in the year prior to the measurement year with result > 4.0 ng/mL (or indication of abnormal test)*  lab_psa  Lab_elevated_psa  *Prescription for 5-alpha reductase inhibitor*  med_a_reduc_inhibit |
| Ultrasound for abdominal aortic aneurysm | Men aged 66-75 years with history of tobacco use  current or past smoker:  dx_tobacco_use  med_tobacco_cessation  ref_smoking_cessation_clinic  soc_past_smoker  soc_smoker  soc_smoker_heavy  soc_smoker_heavy_former  soc_smoker_light  soc_smoker_light_former  soc_smoker_moderate  soc_smoker_moderate_former  soc_smoker_pack_years soc_smoker_years_total  soc_tobacco_cessation  soc_tobacco_current soc_tobacco_past | % men 65-75 who have ever smoked who received 1-time screening for AAA  Abdominal US or other abdominal imaging performed on or after 65th birthday or during measurement period  OR presence of at least 1 AAA in past | gender_male  proc_aaa_screen  proc_abdominal_ct  proc_abdominal_mri  proc_abdominal_us  dx_aaa | soc_non_smoker  soc_tobacco_non_never  doc_hospice  dx_palliative  *within past 6 months*  proc_chemotherapy  *within past 3 months*  doc_nursing_facility |
| Osteoporosis | Women aged 66-75 years of age | % of women 65-75 years of age who received osteoporosis screening  One or more osteoporosis screening tests on or between the patient's 65th birthday and measurement period | gender_female  proc_bmd | dx_osteoporosis  pmh_osteoporosis  med_osteo_prolia  med_osteo_reclast  med_bisphosphonate  med_osteo_tymlos  doc_hospice  dx_palliative  *Exclude if aged 66 and older with BOTH frailty and advanced illness during measurement period*  dx_frailty  dx_advanced_illness |

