| Advance Care Planning | Aged 66 and older | % of patients aged 66 and older with documentation of advance care planning | soc_adv_directive | N/A |
| Hepatitis C | Aged 18-79 years of age | % of patients who received one-time hepatitis C screening | lab_hepatitis_c_ab  lab_hepatitis_c_rna  lab_hepatitis_c_genotype  lab_hepatitis_c_screen | dx_hepatitis_c  dx_hepatitis_c_acute  dx_cirrhosis  dx_hepat_carcinoma  dx_decomp_cirrhosis  dx_esophageal_var  dx_hepatic_encep  dx_ascites  doc_hospice  dx_palliative |
| Depression | 1) Entire cohort    2) Those in cohort 1 with positive finding for depression in the past 12 months  dx_depression  dx_depression_major  doc_phq9_gt9 | 1) % of patients who were screened for depression in the past 12 months  2) For those screening positive for depression, % that received follow-up care within 30 days of a positive screen | doc_depression_score  doc_depression_screen  doc_depression_screen_maternal  doc_phq2_score  doc_phq2_screen  doc_phq9_score  doc_phq9_screen  doc_depression_plan  med_antidepressant  med_antidepressant_monotherapy  ref_mental_hlth_psych  ref_behavioral_health_clinic  visit_behavioral_health  ibh_med_antidepressant | dx_bipolar_disorder  *Depression that starts during past 12 months*  dx_depression  dx_depression_major  dx_mental_beh_dis  doc_hospice  dx_palliative |
| Alcohol use | 1) Entire cohort  2) Those in cohort 1 with positive finding for unhealthy alcohol use  soc_alcohol_use_disorder  dx_alcohol_related_disorders  doc_audit_score | 1) % of patients who were screened for alcohol use one or more times within the past 24 months  2) % of patients in Cohort 1 who  screened positive and received an intervention on or up to 60 days after the date of the first positive screen (61 days total) | doc_audit_screen  doc_audit_score  soc_alcohol_screen  soc_alcohol_use_current  soc_alcohol_use_former  soc_alcohol_use_disorder  soc_alcohol_use_none  med_antialcohol  soc_alcohol_counsel_plan  soc_substance_abuse_counsel  ref_alcohol_rehab  ref_drug_addiction_mgmt  ibh_med_antialcohol | soc_alcohol_use_disorder  dx_alcohol_related_disorders  dx_dementia  doc_hospice  dx_palliative  *Exclusion only for cohort 2*  soc_alcohol_use_none |

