| Tobacco use | 1) Entire cohort  2) All patients in cohort 1 identified as tobacco users  3) Entire cohort | 1) Screened for tobacco use at least once within 24 months  2) % of patients in Cohort 1 who were identified as tobacco users who received tobacco cessation counseling  3) % of patients who were screened for tobacco use within 24 months AND if screened positive, received intervention on or up to 60 days after the date of the first positive screen (61 days total) | dx_tobacco_use  soc_non_smoker  soc_past_smoker  soc_smoker  soc_smoker_ecigarette  soc_smoker_heavy  soc_smoker_heavy_former  soc_smoker_light  soc_smoker_light_former soc_smoker_moderate soc_smoker_moderate_former soc_smoker_pack_years  soc_smoker_years_total  soc_tobacco_cessation  soc_tobacco_current  soc_tobacco_non_never  soc_tobacco_past  soc_tobacco_screen  soc_tobacco_unspecified  med_tobacco_cessation  ref_smoking_cessation_clinic  soc_tobacco_cessation | doc_hospice  dx_palliative |

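### Table 2 and the extraction Appendix give different look-backs for tobacco and alcohol screening within the composite primary endpoint, and the favourable direction of PSA testing at age 70 and over is left undefined

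*Protocol*

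**What the plan says.** **Tobacco and alcohol.** Table 2 (Section 4) has the rows "Tobacco use | Yearly | All adults | A" and "Alcohol misuse | Yearly | 18 or older | B". The Appendix (Section 13, Data Extraction Elements) applies both items to the entire cohort. It scores tobacco as "Screened for tobacco use at least once within 24 months" and alcohol as the share "of patients who were screened for alcohol use one or more times within the past 24 months".

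**Which source governs.** Sections 4, 9.2, 10.1 and 10.3 point to Table 2 for the services assessed. Section 11.8.1 points to the Appendix for the elements to extract. Section 10.3 hands inclusion and exclusion criteria for each service to HEDIS and CMS specifications. The Table 2 footnote allows changes that follow the guidelines in force at data collection. Table 7 in Section 10.4.3 cites Table 4 for the list of services, but Table 4 is the power table.

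**Composite.** The score is the percentage of a patient's recommended services that are up to date, out of at most 12 (Sections 4 and 10.1).

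**PSA.** For men aged 70 and over, Table 2 says "Not recommended if >=70" and assigns grade D, which its footnote defines as a recommendation against the service. The Appendix has one PSA row: the percentage of "men 70 and over who were screened for prostate cancer", with the PSA laboratory codes in the inclusion/numerator column. There is no PSA metric for ages 55-69. Section 10.1 hypothesises "a greater percentage of patients who are up to date on each of the individual preventive health services" in Table 2, without exception.

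**The concern.** Tobacco and alcohol screening carry grades A and B in Table 2 and apply to every patient in the Appendix, so they fall within the recommended services that make up the composite. A primary endpoint whose components have two look-backs has two values for the same patient. If the choice is made after outcome data have been seen, it can be influenced by them. The longer window also carries pre-switch screening into post-switch measurements, which matters at the 12-month assessment.

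The PSA issue is one of direction. The only extracted metric counts tests in the age group for which the protocol's own table grades the service D, and the secondary hypothesis predicts a rise for every service in that table. Unless a direction is stated, a rise in such testing could be reported as support for the intervention.

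**Working it through.** **1. Is the 24-month window a general Appendix convention?** No. Depression screening is also yearly in Table 2, and the Appendix scores it over 12 months. Only tobacco and alcohol move from yearly to 24 months.

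**2. Does another clause settle it?** The HEDIS/CMS sentence covers who enters and leaves each cohort. That can explain some age differences between the two lists (bone density 65 and over against 66-75, pneumococcal 65 against 66, Pap 21-65 against 24-64), but not a numerator look-back. The footnote covers guideline updates only. The zoster numerators also differ: two doses in Table 2; one dose of one product or two of another in the Appendix.

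**3. The stated maximum of 12.** Applicable services were counted by sex and single year of age from 50 to 95, with men taken as ever-smokers.
- Appendix ages: women aged 66-74 reach 12 (influenza, tetanus, zoster, pneumococcal, colorectal, mammogram, bone density, hepatitis C, alcohol, tobacco, depression, advance care planning). Men reach 11 without PSA, and 12 at ages 70-75 with it.
- Table 2 ages: a woman aged 65 reaches 13, because Pap runs to 65, bone density starts at 65, and advance care planning has no age limit.

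The figure of 12 therefore fits the Appendix ages, but it does not show whether PSA is in the composite.

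**4. Difference in level.** Assume a share p is screened in any year, independently between years. The 24-month rate exceeds the 12-month rate by [1 - (1 - p)²] - p = p(1 - p). With two such items among n services, the composite differs by 2p(1 - p)/n. Take n = 12 (the stated maximum) and n = 8 (Section 10.2 assumes an average above 8).
- p = 0.3: 0.21 per item; 3.5 points (n = 12) to 5.3 points (n = 8)
- p = 0.5: 0.25 per item; 4.2 to 6.3 points
- p = 0.7: 0.21 per item; 3.5 to 5.3 points
- p = 0.9: 0.09 per item; 1.5 to 2.3 points

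**5. Effect on the treatment contrast.** Let yearly screening rise from p0 to p1 at the switch. Twelve months later the 12-month rule shows p1 - p0. The 24-month rule shows [1 - (1 - p0)(1 - p1)] - [1 - (1 - p0)²] = (1 - p0)(p1 - p0). At p0 = 0.5 half the effect on that item remains; at p0 = 0.7, 30% remains.

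For a 10-point rise in each item (Section 10.2 calls 10% meaningful for all outcomes), the loss per item is 10 × p0 points, and the composite loses 2 × 10 × p0/n. That is 10/12 = 0.8 to 10/8 = 1.3 points at p0 = 0.5, and 14/12 = 1.2 to 14/8 = 1.8 points at p0 = 0.7.

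If the 12 months run from the end of the 6-month implementation period, only 24 - 18 = 6 of the 24 months, a quarter of the window, lie before the switch.

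**6. PSA.** For a man aged 70-75 with 8 of 11 other services done, the score is 8/11 = 72.7% with PSA left out, 9/12 = 75.0% if a test counts as done, and 8/12 = 66.7% if PSA is in the denominator and untested. The protocol does not say which applies.

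**The case against.** **Which table operates.** Table 2's column is a guideline summary of recommended frequency, and the Appendix is the named list of extraction elements, so one can infer that the Appendix is operative. That narrows the ambiguity. It does not remove it, because the endpoint and hypothesis sections cite Table 2.

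**PSA.** A reader might infer that PSA testing at 70 and over is counted as success and raises the composite. The documents do not support that. Table 2's title says that it covers evidence for and against use, the composite is limited to recommended services, and the PSA row speaks only of being screened, whereas the vaccine rows speak of being up to date. The row's exclusions (prostate cancer, an earlier abnormal result, 5-alpha reductase inhibitors) also suit a measure of avoidable testing. Detailed component scoring could be left to an analysis plan. What stands is the unqualified hypothesis in Section 10.1, which is in the protocol itself and conflicts with grade D when read literally.

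**Dilution.** A reader might infer that a 12-month result under the 24-month rule rests half on pre-intervention screening. Half the window is not half the result. With a constant yearly rate p, the share of positives resting only on the older year is (1 - p)/(2 - p): 41%, 33%, 23% and 9% for p = 0.3, 0.5, 0.7 and 0.9. Twenty-four months after the switch, the window holds no pre-switch time. Carry-over is also inherent in other items, such as colonoscopy and tetanus.

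**Size.** It is tempting to set the level difference against the 10% target. They are different quantities: a rule applied to both control and intervention periods shifts both, and much of the shift cancels. Nor does a gap near 10 points follow under independence, since p(1 - p) cannot exceed 25%.

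**Conclusion.** The look-back conflict is real and sits in a primary endpoint: tobacco and alcohol are yearly in Table 2 and 24-month in the Appendix, with no rule of precedence. The composite level differs by roughly 1.5-6 points between the two rules, assuming yearly screening of 30-90%, independence between years, and 8-12 applicable services. If the same patients are screened every year the gap is smaller; if screening tends to alternate between years it is larger. The protocol gives no screening rates.

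The 24-month rule can attenuate the effect 12 months after the switch. This is marked for the two individual secondary endpoints and modest for the composite, about 1-2 points in the illustration with starting rates of 50-70% and a 10-point rise per item.

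On PSA, the supportable conclusion is limited. The favourable direction and the place in the composite at age 70 and over are not stated, and Section 10.1 read literally would treat more grade-D testing as confirmation. Which clinical interval or age limit is correct is not judged here.

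**What to change.** Before the next extraction, reconcile Table 2 with the Appendix so that a single table gives each component one binding cohort, look-back and numerator, and state that it governs both the composite and the individual endpoints. Start with tobacco and alcohol, then settle the other rows that differ, and correct the Table 4 reference in Table 7.

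For PSA at age 70 and over, state that it lies outside the recommended-services composite, exempt it from the hypothesis of a rise in Section 10.1, and report it separately as a measure for which an increase is not favourable, in line with the protocol's own grade D.

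The cost is an amendment to Table 2, the Appendix, Section 10.1 and Table 7. No new data are needed: the Appendix already reaches back 24 months for tobacco and alcohol, so either window can be computed provided screening dates are kept.
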